### ***Absolute contraindications***

**The device must not be used if the patient has any of the following symptoms:**

- Acute, pronounced pain symptoms despite conventional pain therapy
- Adaptability and patient's position: Do not carry out any training session using the system if it is not possible to adapt the device to the individual physiological patient's position (e.g., in the event of contractures or severe spasticity (stiff/immobile joint) in

the area of the lower extremity, extremely disproportionate growth of the legs and/or spinal column).

- Body weight of less than 15 kg or more than 180 kg
- Body height of less than 100 cm or more than 200 cm
- Insufficient compliance e.g., patients with a serious mental illness or severe neurosis
- For patients with a significant reduction in bone density (osteopenia or osteoporosis), the training is contraindicated. Due to the forces acting on the lower extremities, LEXO® training must not be carried out for patients whose history indicates a significant loss of bone density or an increased risk of fracture (e.g., for people with long-term limited weight bearing), and/or for patients who have already been diagnosed with a significant loss of bone density.
- Osseous instability (non-consolidated fractures, osteogenesis imperfecta, unstable spinal column, pseudoarthrosis)
- Cardiac contraindications
- Use of ventilators
- Highly pronounced vascular diseases of the lower limbs
- High-grade ataxia
- Skin lesions in areas which get in contact with the device or the harness system (decubitus)
- Severely limited range of movement of the lower extremity (e.g., fixated joint contractures, joint arthrodesis) for which even the lightest passive movement training already represents a risk of injury
- States of health preventing active rehabilitation (e.g., respiratory diseases, pregnancy, orthopedic diseases, cognitive impairments restricting communication, neuropsychological disorders, infections or inflammatory diseases, osteomyelitis)

### ***Risk factors (relative contraindications)***

Each patient must be assessed individually by the study PI to determine whether the LEXO® robotic gait trainer is suitable for the patient in the event of:

- Apraxia
- Arthritis in the area of the joints of the lower extremity
- Risk of autonomic dysreflexia (AD) in patients with spinal cord injury (SCI) (severity TH6 or above; an AD occurred in the past increases the risk of a new episode)
- Reduced compliance, such as patients with cognitive impairments, medication
- Uncooperative or (self)aggressive behavior (e.g., transitory psychotic syndrome)

- Cardiac diseases, e.g., heart failure and thoracotomy, uncontrolled orthostatic hypotension or other circulatory problems, circulatory disorders of the lower limbs
- Recent joint injury/endoprosthetics (e.g., total endoprosthetics, knee or hip joint replacement, reconstruction of the cruciate ligament or meniscus) with contraindicated ranges of movement or load limits
- Consolidated fractures in the area of the lower extremity
- Epilepsy
- Infections/swellings/skin ulcers/late effects of previous injuries, especially of the lower extremity
- Recently occurred seizures or increased risk of seizures
- Mechanical ventilation
- Lack of head control
- Long-term infusions (e.g., Baclofen pump, intrathecal pumps, PEG tube ...) or stimulators (e.g., pacemakers, nerve stimulators)
- Enterostomy/ostomy/anus praeter
- Osteoporosis
- Sensory impairments of the lower extremities and the torso, especially reduced sensation of pain. Patients with sensory impairments might not be able to give feedback on possibly occurring pain.
- Skin problems: Before and after every training session, it is a requirement to watch out for wounds and pressure marks either resulting from the training or that were already there, especially in those areas of the body regions which are in contact with the device.
- Pregnancy
- Uncontrolled instability of the hip, knee or ankle joint which would represent a risk despite using the body weight support.

### **3.7. Training, usage and safety aspects of using the investigational medical device**

#### ***Tyromotion Training concept with respect to usage of the LEXO®***

The LEXO® is a complex, technical device. For the safety of the patients, the users and the device itself as well as a successful training, users of the LEXO® gait trainer must be trained beforehand have read the user manual. Reading the manual alone does not convey enough competence for handling the LEXO® gait trainer.

Trained operators, who are responsible for the LEXO®, are obliged to urge personnel, patients, and other persons who are in the environment of the device to fully comply with the safety precautions stated herein. The system may only be operated by properly trained operators. It will be ensured that the system is not manipulated by unauthorised persons. The system must (and will) be unpacked and installed by service representatives authorised by TYROMOTION GmbH only. The system will exclusively be trained by TYROMOTION GmbH authorized trainers. Independent commissioning of the device before training is not permitted and will not be done.

Prospective users must have basic medical training as a prerequisite (e.g., physiotherapy). TYROMOTION GmbH rejects any liability for damage that arose in connection with a training session that was not performed by a trained user. The delivery of the LEXO® includes a structured training for future users. In the case of this clinical investigation, extra training will be provided for a selected team of physiotherapists of the Reha Zentrum Münster to guarantee an optimal use of the device during the clinical investigation. In addition, users (physiotherapists within the clinical investigation team) will perform repeated trainings with the LEXO®. Users must not allow other people to use the LEXO® or instruct other members of the rehabilitation team. Users will be trained by a member of TYROMOTION GmbH or through a trained instructor delegated by TYROMOTION GmbH. The study team will also be thoroughly informed on any contraindications in order to not carrying out the therapy using the LEXO®.

The training content will include:

- LEXO® system / component overview
- Function and application overview
- Indications and contraindications
- Adjustment options and safety instructions for gear unit
- Connection system
- Transfer to the LEXO® system
- Therapy with the LEXO® system
- Functionality of the emergency lowering system and warning notices
- Cleaning the device

### ***Safety aspects of using LEXO®***

Any warnings with respect to a safe use of LEXO® are specified in detail in the user manual. Additionally, the patient will be explained that he or she may use an emergency STOP button to interrupt the power supply of the drives. The study team will undergo a structured training by Tyromotion.

Residual risk

Despite all safety precautions, there can be unforeseeable residual risks when carrying out a therapy session using the LEXO®. Even if the device is used properly, the patient or operator may still suffer from minor pinch or crush injuries in rare cases. A detailed risk analysis has been described in Chapter 1.2.

### 3.8. Device approval status

The LEXO® robotic gait trainer is approved in Austria and has gained an EC-Certificate regarding a Full quality assurance system. The certificate states that Tyromotion has implemented and maintains a full quality assurance system which applies to the products at every stage from design to final controls.

Through an audit, documented in a report, it was verified that the management system fulfills the requirements of Annex II – excluding Section 4 of Council Directive 93/42/EEC concerning medical devices with respect to the LEXO®. The LEXO is classified as a class IIa medical device.

As stated in Chapter 3.4. “Identification and traceability of the investigational medical device”, according to the Declaration of Conformity the name of the investigational medical device is LEXO®.

Conformity has been assessed in compliance with RL 93/42/EWG/ processes (RL 93/42/EEC Annex II without Sec. 4). The EC-Verification Certificate, Annex II.

Compliance with harmonized standards was assessed and demonstrated as shown in Table 4. The manufacturer Tyromotion declares under sole responsibility that the LEXO® as delivered are in compliance with directive 93/42/EEC and the Austrian medical- device-law BGBl. 657/1996. The LEXO® is CE marked.

**Table 4:** Used harmonized standards

|                                                                                                                                                                                             |                                                                                                                     |
|---------------------------------------------------------------------------------------------------------------------------------------------------------------------------------------------|---------------------------------------------------------------------------------------------------------------------|
| EN 60601-1:2006 + Cor.:2010 +A1:2013
EN ISO 13485:2016 + AC:2016
EN 14971:2012
EN 62366-1:2015 + A1:2015
EN 62304:2006 + Cor.:2008 + A1:2015 | EN 60601-1-2:2015
EN ISO 10993-1:2009
EN ISO 15223-1:2016
EN 1041:2008+A1:2013 |
|---------------------------------------------------------------------------------------------------------------------------------------------------------------------------------------------|---------------------------------------------------------------------------------------------------------------------|

## 4 STUDY DESIGN AND PROCEDURES

### 4.1. General aspects, justification and study related procedures

This clinical investigation protocol follows the Standard Protocol Items for Clinical Trials (SPIRIT; Statement 2013) (Chan et al., 2013), the World Medical Association (WMA) Declaration of Helsinki - Ethical Principles for Medical Research involving human subjects (2013) (WMA, 2013), the Guidelines of the International Organization for Standardization (ISO), ICH E6 Guideline for good clinical practice (2016) and Guideline for Clinical investigation of medical devices for human subjects - Good clinical practice (ISO/DIS 14155:2018) (2018).

A prospective comparative multiple case study design with mainly quantitative data but also qualitative data analyses and a cross-case analysis will be used. A multiple case-oriented research strategy will be adopted to acquire knowledge about the outcomes from RAGT within the 8 different patient (disease) groups, learn about similarities and differences between individual cases and neurological disorders within study intervention periods and emerging patterns (Ababacar et al., 2020; Nordbeck, 2013). The synthesis across cases will extend beyond the comparison of similarities and differences to generate information on the reasons and explanations as to the findings from the RAGT intervention. That is, the prospective comparative multiple case study design will allow for theory development with regard to causality to inform the hypotheses of a follow-up randomised controlled trial (Goodrick, 2014). In other words, except some degree of comparison that will be fundamental to the comparative multiple case study design, a distinctive feature of this study type is the emphasis on examining causality i.e., the extent to which the RAGT intervention caused the outcomes (Goodrick, 2014).

In practice, this comparative multi case study will involve the analysis and synthesis of the similarities, differences and patterns across multiple cases, with the shared common goal of gaining knowledge about the feasibility, acceptability and preliminary effects of RAGT. Case selection will be performed using two different strategies: within disease groups, the 'Most Similar Systems Design' (MSSD) will be applied and between disease groups, the 'Most Different Systems Design' (MDSD) (Anckar, 2008; Przeworski & Teune, 1970) will be used, considering the 8 neurological disease groups with different symptom complexes involving distinct central and peripheral nervous system (CNS, PNS) sensorimotor system areas and pathways (upper and lower motor neurons including both the cerebrum and spinal cord, extra pyramidal motor system, peripheral nervous system and cerebellum). As for MSSD, it will mean to purposively choose study patients that are similar in as many background characteristics as possible, but without systematically matching cases on all the relevant control variables. As for MDSD, the strategy will be to purposively select patients that are as different as possible with respect to extraneous variables. The basic logic is that differences cannot explain similarities (Przeworski & Teune, 1970). Both a quantitative and qualitative data collection and analyses will be used to achieve these goals.

All cases will receive RAGT training using a standard protocol that will allow individualisation according to the neurological disease, functional status and walking performance of the patient, the stage of the disease, age of the patient etc. No control intervention will be used because this is the first study to compare a LEXO-based RAGT in patients with 7 different neurological disorders, one of them including patients at different stages of recovery and functional status (subacute, severe stroke and chronic, mild to moderate stroke).

Figure 4 presents a sample flow diagram of the clinical investigation including analyses.

[figure not shown]

**Figure 4:** Sample flow diagram of the clinical investigation including analyses

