## **2 PURPOSE, OBJECTIVES AND HYPOTHESES OF THE CLINICAL INVESTIGATION**

### **2.1. Study purpose**

The purpose of this clinical investigation is to investigate the feasibility and acceptability and compare the preliminary effects of RAGT a mixed population with neurological diseases consisting of patients with stroke in the subacute and chronic phases and with severe and mild to moderate disability, MS, Parkinson's Disease, spastic para-or tetraplegia, mild to medium grade hereditary ataxia, acute or chronic inflammatory demyelinating polyneuropathy and motoneuron disease. A further purpose of this clinical investigation is to synthesise quantitative and qualitative results for examining causality i.e., the extent to which the RAGT intervention may have caused the outcomes.

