## **5 PARTICIPANTS**

### **5.1. Sampling and participant recruitment**

Stratified sampling will be used in this clinical investigation, with eight strata representing the different neurological diseases, as well as patients post stroke in the subacute and chronic phases who are severely and mild to moderately affected, respectively. This strategy will be chosen based on the primarily quantitative nature of this study.

All patients with a first-ever ischemic or hemorrhagic stroke, multiple sclerosis (MS), Parkinson's Disease (PD), a spastic para- or tetraplegia caused by any type of spinal cord lesion, mild to medium grade hereditary ataxia, acute or chronic inflammatory demyelinating polyneuropathy (e.g., GBS, CIDP) or a motoneuron disease (e.g., ALS) treated at the Reha Zentrum Münster during the recruitment period will be checked by the medical staff with regard to their suitability for participation in the clinical investigation. All patients who meet the inclusion criteria of this study and do not meet any of the exclusion criteria will be informed verbally and in writing about the study by the PI or investigator. After determining the general eligibility (inclusion criteria) and the consent of the patient i.e., their interest in participating in the study, a screening will be carried out. Using predefined criteria for intact cognitive functioning, with a cut-off score  $\geq 24/30$  points on the Mini Mental State Examination (MMSE) (Folstein et al., 1975), patients with moderate to severe cognitive impairment will be excluded. Furthermore, patients without walking impairment as defined by a neurological exam and an FAC score of 5 will be excluded. In the absence of these exclusion criteria, the study inclusion described below will take place.

After having provided the patient with the patient information sheet, an appropriate period of reflection for the patient, the opportunity for queries and answers and the patient's consent to participate, the informed consent form will then be dated and signed by both the patient and the doctor. The investigator will note the participation on a specific patient identification list. It will be used to later identify the patient and contain the identification number (ID), the full name of the patient, the date of birth and the date of admission to the clinical investigation. The patient identification list will remain at the trial centre after the clinical investigation has been completed.

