## **8. STATISTICAL DESIGN AND ANALYSIS**

### **8.1. General aspects of the analysis**

The analysis of this comparative multiple case studies uses mixed methods, integrating quantitative and qualitative data. These data will be analysed together with the intention of gaining an in-depth understanding of the cases. In addition, the use of mixed methods will purposefully be adopted to generate causal propositions. A comparison of the walking, balance, and other outcomes within the cases of one stratum (disease group) and between the cases (disease groups) will be at the heart of the comparative approach.

A single case can also be the source of new insights about critical success factors. For example, it may become apparent that RAGT has improved walking in one patient but failed in others. Therefore, such a case may be selected and the attributes and features that may be responsible for the differences explored in more depth. In addition, triangulation will be used in evaluation to check answers to descriptive questions about the way things are, for example, by confirming semi-structured observations of the intervention with direct measures from LEXO® or standardised subjective observations or motor test performances.

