- Case selection will be performed using two different strategies: within disease groups, the 'Most Similar Systems Design' (MSSD) will be applied and between disease groups, the 'Most Different Systems Design' (MDSD) (Anckar, 2008; Przeworski & Teune, 1970) will be used, considering 8 neurological disease groups with symptom complexes involving distinct sensorimotor system parts of the central nervous system (upper and lower motor neurons including both the cerebrum and spinal cord, extra pyramidal motor system, peripheral nervous system, cerebellum and afferent pathways including their respective representations in the cortex). As for MSSD, it will mean to choose study patients that are similar in as many background characteristics as possible, but without systematically matching cases on all the relevant control variables. As for MDSD, the strategy will be to select patients that are as different as possible with respect to extraneous variables. The basic logic is that differences cannot explain similarities (Przeworski & Teune, 1970).
- The objectives, inclusion and exclusion criteria, endpoints and assessments and study procedures are clearly stated.
- Both a quantitative and qualitative data collection and analyses will be used.
- Mixing methods is a form of triangulation in research seen as mitigating the weaknesses found in single methods (Heale & Forbes, 2013). Triangulation in research is the use of more than one approach to researching a question. The

objective is to increase confidence in the findings through the confirmation of a proposition using two or more independent measures (Noble & Heale, 2019). The combination of findings from two or more rigorous approaches provides a more comprehensive picture of the results than either approach could do alone (Noble & Heale, 2019).

- The intervention of this study uses a standard RAGT protocol but is individualised and hence adapted to the different patient groups (Cases 1-8) and the individual performance level of the participants.
- Structured data documentation, management and evaluation will be used as outlined in this clinical investigation protocol
- Continuous monitoring for adverse events using a structured log and predefined evaluation criteria

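### Protocol 4.1 selects cases and 5.1 informs every eligible patient: the two sampling rules are incompatible, and with the stratum quotas they leave the recruitment rate measuring something other than willingness to take part

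*Protocol*

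**What the plan says.** Section 4.1 describes case selection by two strategies. Within disease groups (Most Similar Systems Design, MSSD) the team will "purposively choose study patients that are similar in as many background characteristics as possible", though without systematic matching. Between disease groups (Most Different Systems Design, MDSD), "the strategy will be to purposively select patients that are as different as possible with respect to extraneous variables". The list under Strengths in section 8.2 (Strengths and Limitations) repeats the rule without the word for purposive choice: "the strategy will be to select patients that are as different as possible with respect to extraneous variables". Neither place names the variables or says who selects and at what step. Both give the same rationale: "The basic logic is that differences cannot explain similarities".

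Section 5.1 gives a different rule: "Stratified sampling will be used in this clinical investigation, with eight strata representing the different neurological diseases". Every patient with a listed diagnosis treated in the recruitment period is checked, and "All patients who meet the inclusion criteria of this study and do not meet any of the exclusion criteria will be informed verbally". Screening follows, then inclusion. No step chooses among eligible patients.

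Section 5.3 fixes quotas of 5 in four strata and 2 in the other four. Section 8.2 (Planned statistical analysis) defines the recruitment rate as consenting patients divided by eligible patients, times 100. Section 2.1 states as one purpose to "compare the preliminary effects of RAGT a mixed population with neurological diseases", and section 8.1 says that comparison within and "between the cases (disease groups) will be at the heart of the comparative approach".

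**The concern.** Staff cannot include every eligible, consenting patient in turn and also choose among them on background characteristics. Which rule is used decides who enters the study, and it changes the meaning of a component of the primary endpoint. A consent rate is useful for planning the follow-up randomised trial because it estimates how many eligible patients agree when asked. If the denominator contains patients who were never asked, because they did not fit a wanted profile or because their stratum was full, the figure mixes willingness with selection and quota size.

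The second stake is the comparison between disease groups. Selecting for maximal difference on extraneous variables widens background differences between groups. The stated logic then allows a conclusion from a response that unlike groups share, but not an explanation of why groups respond differently. The protocol nevertheless plans to interpret both similarities and differences and to pass the resulting theory to the randomised trial.

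**Working it through.** **Quotas.** Section 5.3: 4 × 5 + 4 × 2 = 28, which reproduces the stated sample size. The protocol contains no power calculation to reproduce.

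**The two rules side by side.** Section 4.1 needs a choice among eligible patients, on variables it does not name. Section 5.1 informs all eligible patients and moves from screening to inclusion with no choice in between. No sentence ranks one rule above the other.

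**Recruitment rate.** Let c be the consent proportion among patients approached and f the fraction of eligible patients who are approached. Under the definition in section 8.2, the reported rate is c × f. It equals c only when f = 1.

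Assumptions, since the protocol gives neither value: c = 0.80, and 28 consenting patients, so 28 / 0.80 = 35 are approached.

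- With f = 2/3: 0.80 × 2/3 = 0.53, so 80% willingness is reported as 53%.
- Over a range of eligible totals, with Wilson 95% intervals (the protocol's own method):

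| Eligible patients | f | Reported rate | 95% interval |
|---|---|---|---|
| 35 | 1.00 | 80.0% | 64.1 to 90.0 |
| 45 | 0.78 | 62.2% | 47.6 to 74.9 |
| 56 | 0.63 | 50.0% | 37.3 to 62.7 |
| 70 | 0.50 | 40.0% | 29.3 to 51.7 |
| 100 | 0.35 | 28.0% | 20.1 to 37.5 |

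The arithmetic is the same whether the patients who were not approached were passed over under 4.1 or came after their stratum was full. Ten late arrivals alone (35 + 10 = 45) move 80% to 62%. The quota effect therefore arises under 5.1 as well.

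**Differences between disease groups.** Simulation with strata of 5, 5, 5, 5, 2, 2, 2, 2, no true disease effect, and one covariate that explains a share R² of the variance in change. The index is a one-way F test (7 and 20 degrees of freedom) at 5%, used only as a yardstick.

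- Covariate fully separated between groups: a difference is declared in about 9%, 14%, 28% and 46% of studies at R² = 0.05, 0.10, 0.20 and 0.30.
- No selection, but diseases naturally differ on the covariate (between-disease share of its variance assumed to be 30%, 50% or 70%): about 7%, 9% and 11% at R² = 0.10, and about 9%, 14% and 18% at R² = 0.20.

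So the excess that selection could cause, even at full separation, is about 14 − 11 = 3 to 14 − 7 = 7 percentage points at R² = 0.10, and 28 − 18 = 10 to 28 − 9 = 19 points at R² = 0.20.

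**The case against.** A reader might infer that the protocol deliberately aligns disease with age, severity and disease duration, so that purposive selection confounds the whole between-group comparison. The text does not support that. Section 4.1 names none of these variables, rules out systematic matching, and introduces MDSD by reference to eight disease groups with different symptom complexes. A milder reading, that MDSD only describes the choice of unlike diseases, is possible, although the sentence itself speaks of selecting patients on extraneous variables.

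Much of the confounding is also built into the strata and would survive any sampling rule. Stroke is split into severe subacute and mild-to-moderate chronic, motor neuron disease is limited to the early active stage, and ataxia to mild or moderate. Disease groups are analysed descriptively; the only inferential analysis is the pooled pre-post comparison. The Limitations list acknowledges that efficacy cannot be tested by disease group and that there is no control group. Purposive selection is legitimate in a multiple case study, and for the aim of judging whether the training caused the outcomes, a response shared by unlike groups is what MDSD can support.

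On recruitment, if 5.1 is followed nobody is passed over for profile, so that part of the harm is conditional on 4.1 being applied. Also, section 4.8 sets its recruitment success criterion in patients per month, so no pass mark hangs on the percentage.

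All of this stands as a limit on size. It does not remove the conflict between 4.1 and 5.1, the unnamed variables, or the lack of a rule for eligible patients who are not approached. Because the sampling rule governs enrolment, it has to be settled in the protocol.

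**Conclusion.** The two sampling rules are incompatible, and the recruitment rate is not interpretable until one is chosen and the denominator is defined. The reduction from 80% to 53% rests on two assumed inputs, 80% consent and two thirds picked. It shows the mechanism and does not predict the trial's rate. The quota effect does not depend on which rule is followed.

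For the comparison between groups, the supportable statement is limited. Selection for maximal difference would add to differences that exist anyway, and the protocol's own logic does not extend to explaining why groups differ. The 9% to 46% figures are at most an upper bound: they assume full separation of all eight groups and concern a test that the plan does not run. They should not be read as the error rate of this study. The point merits a wording change before enrolment and does not invalidate the study.

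**What to change.** Keep one sampling rule. In 4.1 and the Strengths list, remove MSSD and MDSD as methods of choosing patients. In 5.1, state that all eligible patients are approached consecutively within each of the eight strata until its quota of 5 or 2 is full.

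Log every eligible patient who is not approached, with the reason, including arrival after the quota was full. In 8.2 (Planned statistical analysis), define the recruitment rate as consenting patients divided by eligible patients approached while their stratum was open, and report the number of eligible patients not approached beside it.

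Keep MSSD and MDSD as a framework for reading the finished cases. Similar outcomes across unlike groups may be interpreted; differences between groups are reported descriptively beside baseline characteristics and not attributed to disease.

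The cost is wording in 4.1, 5.1, 8.2 and the Strengths list, plus log entries, with no extra patients or procedures. Patients within a stratum may be somewhat less alike, and the confounding inherent in the strata remains.
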